## Abstract

**Background:**

Recently, validated risk models predicting adverse obstetric outcomes combined with risk-dependent care paths have been made available for early antenatal care in the southeastern part of the Netherlands. This study will evaluate implementation progress and impact of the new approach in obstetric care.

**Objective:**

The objective of this paper is to describe the design of a study evaluating the impact of implementing risk-dependent care. Validated first-trimester prediction models are embedded in daily clinical practice and combined with risk-dependent obstetric care paths.

**Methods:**

A multicenter prospective cohort study consisting of women who receive risk-dependent care is being performed from April 2017 to April 2018 (Expect Study II). Obstetric risk profiles will be calculated using a Web-based tool, the Expect prediction tool. The primary outcomes are the adherence of health care professionals and compliance of women. Secondary outcomes are patient satisfaction and cost-effectiveness. Outcome measures will be established using Web-based questionnaires. The secondary outcomes of the risk-dependent care cohort (Expect II) will be compared with the outcomes of a similar prospective cohort (Expect I). Women of this similar cohort received former care-as-usual and were prospectively included between July 1, 2013 and December 31, 2015 (Expect I).

**Results:**

Currently, women are being recruited for the Expect Study II, and a total of 300 women are enrolled.

**Conclusions:**

This study will provide information about the implementation and impact of a new approach in obstetric care using prediction models and risk-dependent obstetric care paths.

**Trial Registration:**

Netherlands Trial Register NTR4143; http://www.trialregister.nl/trialreg/admin/rctview.asp?TC=4143 (Archived by WebCite at http://www.webcitation.org/6t8ijtpd9)

## Introduction

Perinatal mortality plays a pivotal role in the quality assessment of perinatal care [1]. In developed countries the main causes of perinatal mortality are small-for-gestational-age infancy (SGA), preterm birth (PTB), and asphyxia [2,3]. Pre-eclampsia (PE) is an important cause for both SGA and induced PTB [4]. Risks of asphyxia and birth injuries are increased among infants that are large-for-gestational-age (LGA) [5], which in turn is strongly associated with gestational diabetes mellitus (GDM) [6]. Thus, PE, GDM, PTB, SGA, and LGA are all directly or indirectly related to perinatal mortality.

A number of interventions have shown to be effective in the prevention of adverse pregnancy outcomes, such as calcium suppletion and low-dose aspirin treatment in case of PE [7-9], adequate management of GDM [5,10,11], and progesterone administration in women at risk of spontanous PTB [12]. Besides calcium supplementation, most of these interventions are not suitable for all pregnant women, because of either possible adverse effects, patient burden, or costs. Early prediction of obstetric risks may therefore help health care professionals in designing intervention strategies based on women’s individual risks.

Recently, we performed an external validation study of first trimester prediction models predicting the risk of PE, GDM, PTB, SGA and LGA (the Expect Study I) [13,14]. The Expect Study I identified clinically useful prediction models for PE and GDM. The Limburg Obstetric Consortium (LOC), midwives and gynecologists of the southeastern part of the Netherlands developed care pathways, for example, basic antenatal care for women at low risk and additional risk-dependent care for women with elevated risks of PE, GDM, PTB, SGA, or LGA. The LOC agreed to implement the risk models predicting PE and GDM, in order to identify women at increased risk of these outcomes, and to offer these women risk-dependent care.

The current protocol describes the design of a multicenter prospective cohort study (Expect Study II) evaluating the implementation progress of using these prediction models combined with tailored care paths for PE and GDM.

The primary aims of the Expect Study II are to measure adherence to the new risk-dependent care guidelines by health care professionals and compliance of pregnant women who received recommendations. The secondary aims are to evaluate its impact upon patient satisfaction and cost-effectiveness. Secondary aims will be studied by comparing these outcomes of the Expect II cohort with the Expect I cohort.

## Methods

### Study Design and Recruitment

In April 2017, the Expect prediction tool, was introduced. The Expect prediction tool was developed to enable individual risk assessment during early pregnancy regarding the risks of PE, GDM, PTB, SGA, and LGA. Validated models selected by the LOC to predict PE and GDM have been incorporated into this tool (unpublished study submitted by [name] et al, January 2018). Risk assessment of spontaneous PTB, SGA and LGA is achieved using the revised LOC guidelines [15]. For nulliparous women, the prediction tool comprises 14 variables concerning anthropometric data, relevant medical history, and family history. For multiparous women the tool enquires 6 more variables, all concerning the women’s obstetric history.

The Expect prediction tool is a Web-based form which calculates the estimated risk profiles. This tool was made available for health care professionals via the Expect study website for implementation in daily obstetric care. Besides the estimated risks of adverse pregnancy outcomes, the tool provides recommendations for tailored antenatal care based on personalized risks (ie, risk-dependent care). In addition, patient information brochures relevant to the patient’s risk profile will be automatically generated. The health care professionals can use this tool during one of the pregnant woman’s antenatal visits before 16 weeks of pregnancy. Using a shared decision approach, the appropriate risk-dependent care path with corresponding preventive measures and check-ups will be selected.

In order to implement risk-dependent care successfully, midwives and gynecologists are encouraged to use the Expect prediction tool by representatives of the LOC. The Expect prediction tool is introduced by email to all obstetric health care professionals in the region. Furthermore, oral presentations will be given at every hospital and at local midwifery meetings. Additionally, the hospitals and midwifery practices are contacted regularly by phone and in person to evaluate the Expect prediction tool.

The midwives and gynecologists play a central role in enrolling pregnant women into the Expect Study II, by asking women whether they are interested in receiving further information about participating in the Expect Study II. Almost every pregnant woman is eligible for our study. The exclusion criteria are (1) maternal age <18 years, (2) documented multiple pregnancy, and (3) ≥16 weeks of gestation at intake. The eligibility criteria are identical to those of the Expect Study I cohort [13]. Eligible women agreeing to participate are asked to give informed consent and to complete 4 Web-based surveys at enrolment, 24 weeks and 34 weeks of gestation, and 6 weeks after due date.

A personal link to the first online survey will be sent immediately after enrolment. If the survey was not accessed or incomplete, 2 automatic reminders will be sent by email at 3-day intervals for surveys one to three and at 6-day intervals for the postpartum survey. In case of non-response, women will be contacted by phone (provided that a correct phone number is available). If women report PTB at the beginning of survey two or three, they will automatically be redirected to the postpartum survey.

The medical ethical committee of Maastricht University Medical Centre evaluated the study protocol and declared that the study did not fall within the scope of the Dutch Medical Research Involving Human Subjects Act (WMO; METC-17-4-057).

### Tailored-Care Paths

The LOC consists of midwives (n=9), gynecologists (n=9), professionals in maternity care (n=2), researchers (n=3), and an independent chairman. They meet four to five times annually and represent the University medical school, midwifery academy, all hospitals, and roughly 80% (n=90) of the midwives of the province. The midwives and gynecologists of the LOC revised the content of obstetric care. We will briefly describe the most important changes regarding antenatal care compared to former care-as-usual which has been observed during Expect Study I. All women will receive basic antenatal care. In the new tailored care paths, recommendations about calcium and vitamin D supplementation are emphasized for all women and an additional ultrasound for fetal growth assessment at 32 weeks of pregnancy is introduced as part of basic antenatal care.

An overview of the care pathways is provided in Table 1. Additional risk-dependent care for women with a mildly elevated risk of PE comprises the recommendation of preventive aspirin treatment, 80-100 mg aspirin daily from 12 weeks up to 36 weeks of pregnancy. Obstetric care for women with a substantial risk of PE additionally comprises of extended blood tests, blood pressure measurements every 2 weeks from 14 weeks up to 40 weeks of gestation, and 2 additional ultrasounds for fetal growth measurements.

Women with a history of GDM are advised to have an oral glucose tolerance test (OGTT) at 16 and 26 weeks of pregnancy. Women with a mildly elevated risk are advised to have an OGTT at 24 weeks of pregnancy. Furthermore, in both cases, women will receive two additional ultrasounds for fetal growth measurements in addition to basic antenatal care.

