### Statistical Analysis

Missing values will be handled by imputation. Stochastic regression imputation with predictive mean matching as the imputation model will be used to prevent biased results based on complete case analysis only [19].

Adherence will be calculated by the proportion of women who reported to have received the LOC recommendations regarding adequate vitamin D and calcium intake, preventive aspirin treatment, and OGTT. Answers of participants will be linked to their estimated risk profile based on the Expect prediction tool.

Compliance will be analyzed by calculating the proportion of women who complied with the recommendations received from their health care professional regarding aspirin treatment, OGTT, vitamin D, and calcium intake. Vitamin D is analyzed based on supplement intake and sunlight exposure. Calcium intake is determined by calculating the daily intake from diet and supplement use. Dietary intake will be estimated using answers from a selection of questions from the Dutch National Food Frequency Questionnaire tool [20]. These questions address food products that cumulatively cover >80% of the variance in calcium intake [21]. Total intake of both nutrients will be compared with the recommended intake by the LOC (1000 milligram calcium per day and 10 microgram of vitamin D per day) in order to determine compliance to these recommendations.

The secondary outcomes, patient satisfaction and cost-effectiveness, will be analyzed by comparing Expect Study II with the outcomes of former care-as-usual (Expect Study I). Patient satisfaction scores will be analyzed using multiple linear regression.

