## Discussion

This paper describes the protocol of an impact study regarding the implementation of externally validated prediction models combined with risk-based care pathways in obstetric care. Prediction models are becoming increasingly popular in medicine [26]. Although the number of prediction models being published has increased tremendously in recent years, the number of external validation studies remains small [26]. Furthermore, performances of models predicting adverse pregnancy outcomes and the efficacy of preventive interventions for these outcomes are generally documented separately [8,27,28]. Impact studies, describing the effect of using prediction models in daily practice combined with preventive interventions relevant to the estimated risk are nearly non-existent [26]. To the best of our knowledge no impact studies using prediction models in general obstetric practice have been published.

The strengths of our design are the multicenter prospective data collection and the similarity of both cohorts. Recruitment in multiple centers, hospitals and midwife clinics, improves the probability of collecting a representative sample of the obstetric population. This is essential in the Netherlands, since most pregnant women receive antenatal care by midwives at outpatient clinics [29]. Furthermore, optimal measurement of the outcomes is achieved by prospective data collection [30]. Finally, because the two cohorts are kept as similar as possible, we are able to accurately compare the former care-as-usual with the new risk-dependent care.

Some limitations of the design must also be noted. First, since the comparison of secondary outcomes of Expect II with those of Expect I is essentially a before-and-after comparison, time trends in the outcomes can theoretically influence results. In the interpretation of the results, we will take such trends into account, fro exmaple, by looking at trends in the studied outcomes from other regions in the Netherlands.

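### The Expect II versus Expect I comparison of satisfaction and cost-effectiveness estimates the effect of the whole revised care package, not of the additional risk-dependent care to which the article attributes it

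*Protocol article*

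**What the plan says.** The abstract's Objective reads "The objective of this paper is to describe the design of a study evaluating the impact of implementing risk-dependent care". Two places define that care narrowly. The Introduction distinguishes "basic antenatal care for women at low risk and additional risk-dependent care for women with elevated risks of PE, GDM, PTB, SGA, or LGA". Study Design and Recruitment states that "the tool provides recommendations for tailored antenatal care based on personalized risks (ie, risk-dependent care"). Table 1 follows the same division, with one column for basic care and separate columns for additional risk-dependent care.

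Tailored-Care Paths then describes the main "changes regarding antenatal care compared to former care-as-usual which has been observed during Expect Study I". Some apply only to women at elevated risk: aspirin advice, OGTT, extra blood tests, blood pressure checks and growth scans. Two apply to everyone. The first concerns nutrition: "recommendations about calcium and vitamin D supplementation are emphasized for all women". The second concerns monitoring, where the section reports that "an additional ultrasound for fetal growth assessment at 32 weeks of pregnancy is introduced as part of basic antenatal care".

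Under Statistical Analysis, the secondary outcomes "will be analyzed by comparing Expect Study II with the outcomes of former care-as-usual (Expect Study I"). Data Collection describes the same comparison as one of the effects of risk-dependent care against former care-as-usual. The Discussion claims that "because the two cohorts are kept as similar as possible, we are able to accurately compare the former care-as-usual with the new risk-dependent care".

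**The concern.** On the article's narrow definition, two kinds of change separate the cohorts: one that depends on a woman's risk and one that does not. A whole-cohort difference in cost, QALYs or satisfaction contains both. Adjusting for case mix or for time trends would not separate them, because both changes distinguish the same two cohorts in the same region.

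The stake is how the secondary results are used. The economic evaluation takes a health care perspective, so a scan offered to every woman enters incremental cost directly, although offering it needs no prediction model. A reader deciding whether to adopt model-guided care would take both ICERs as a verdict on it, when part of the cost, and possibly part of any change in satisfaction, comes from changes that do not depend on risk.

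**Working it through.** **1. What differs between the cohorts** (Tailored-Care Paths, Study Design and Recruitment, Table 1)

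| Change from Expect I to Expect II | Who receives it |
|---|---|
| Emphasised calcium and vitamin D advice | all women |
| Growth scan at 32 weeks | all women |
| Risk assessment with the prediction tool, with brochures matched to the risk profile | all women on whom the tool is used |
| Additional PE and GDM care | women at elevated risk |

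Table 1 also shows additional columns for SGA/LGA and spontaneous PTB. The article does not say which of their items are new.

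**2. What the contrast estimates.** Let U be the mean effect of the changes for all women (scan, advice, tool), R the mean effect of the additional paths among women at elevated risk, and π the share of women on such a path. If the effects add up and time trends are set aside, Expect II minus Expect I = U + πR. The Objective, Data Collection and Discussion attribute the whole sum to the term πR. The limitations name time trends and reliance on questionnaires, but not U.

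**3. Can the size of U be stated?** No. Three inputs are missing.
- π: Sample size gives about 30% at elevated PE risk, that is 0.30 × 400 = 120 women, leaving 280. Those 280 may still be on a GDM, SGA/LGA or PTB path, and these shares are not given. A further 20% of women on such paths would bring π to one half.
- Unit costs: none are given.
- The scan count: the text names one new basic scan, at 32 weeks, but Table 1 also lists fetal biometry at 36 weeks under basic care. The two places need to be reconciled on whether that scan is new.

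A count of growth scans shows how open the answer is. Take one new universal scan per woman and two extra scans per woman for an assumed share q. The universal share of added scans is 1/(1 + 2q). At q = 10% this is 1/1.2 = 83%; at q = 50% it is 1/2 = 50%; at q = 70% it is 1/2.4 = 42%. The documents do not give q, and the count leaves out aspirin, OGTTs, blood tests and blood pressure visits. It is not a cost share.

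**4. What a risk-stratified analysis would give.** In women without elevated predicted risk the cohort difference is about U; in women with elevated risk it is about U + R. Subtracting gives R, provided U and any time trend are the same in both groups. The low-risk difference is not the effect of the scan alone, because those women also receive the advice and the risk assessment.

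Precision: with share p at elevated risk in both cohorts and equal variances, the variance of the difference between strata is 1/[p(1 − p)] times that of the overall difference. At p = 0.30 this is 1/0.21 = 4.76, so the standard error is √4.76 = 2.18 times as large. At p = 0.50 the factor is √4 = 2, the most favourable case.

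**5. Sample size.** The article's 400 serves the primary outcomes. With p = 0.21 and half-width 0.04, n = 1.96² × 0.21 × 0.79 / 0.04² = 398, which reproduces it. Adherence and compliance use Expect II alone, so neither they nor this figure is touched.

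**The case against.** The strongest reply is that the package is the intervention. The abstract calls all of Expect II the risk-dependent care cohort. The primary aim concerns adherence to the new risk-dependent care guidelines, and that adherence includes calcium and vitamin D advice for all women. Tailored-Care Paths places both universal changes within the new care paths. On this wider use of the term, Expect II versus Expect I compares exactly what was introduced with what went before. This stands: the contrast is sound for the package. It does not remove the point, because the Introduction, Study Design and Recruitment and Table 1 use the narrower sense, and the reader is never told which sense the cost and satisfaction results carry.

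Two further replies also stand. Low-risk women are exposed to the prediction tool, so the universal and risk-dependent parts do not separate cleanly. And a cost breakdown is commonly left to a fuller plan, so its absence from the article is not itself a fault. The fault is in the attribution that the article does state.

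A reader might also infer that the risk-dependent paths reach only a minority of women, or that the universal scan accounts for most of the added cost. The documents support neither. Only the PE share is given, and there are no unit costs.

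**Conclusion.** The point holds as one of attribution. The cohort comparison estimates the effect of the revised care package against former care. The Objective, Data Collection and Discussion over-attribute it to risk-dependent care as the article itself defines that care, and the limitations omit the change in basic care.

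It would go too far to say that the comparison is invalid or uninformative: it answers the package question, subject to the time trends already acknowledged. The size of the misattribution is unknown. The conclusion needs only that basic care differs between the cohorts, which Tailored-Care Paths states; it does not need the date on which the universal changes began. Its reach is limited to the secondary outcomes.

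**What to change.** 1. In the Objective, Data Collection and Discussion, describe the contrast as revised care package versus former care. Add the simultaneous change in basic care to the limitations.
2. As a secondary analysis, apply the PE and GDM prediction models to both cohorts. Report cost and satisfaction differences for women with and without elevated predicted risk, and compare the two differences. State the assumption that the universal changes and time trends act alike in both groups, and do not present the low-risk difference as the effect of the scan.
3. Where the resource-use data allow, report incremental cost in total and split into universal and risk-dependent items.

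The rewording costs nothing beyond a narrower headline. Step 2 looks feasible, because Expect I was the validation cohort for these models and supplied the 30% figure, but the article describes tool-based risk profiles for Expect II only, so access to the Expect I predictors should be confirmed. Stratum estimates will be less precise: the comparison between strata has at least twice the standard error of the overall difference under the assumptions above. Step 3 depends on whether self-reported resource use can tell a routine 32-week scan from an indicated one, which the article does not say. No new data collection or change in sample size is proposed.

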### Outcome Measures and Measurement

The primary outcomes are health care professionals’ adherence to key recommendations and compliance of the women involved in the study. Adherence is defined as the proportion of women that actually received the key recommendations they should have received from their health care professional according to the LOC guidelines. Adherence will be analyzed regarding recommendations of adequate vitamin D (yes or no) and calcium intake (yes or no) for all women, preventive aspirin treatment (yes or no) for women with elevated PE risks, and OGTT (yes or no) for women with elevated GDM risks.

Compliance is defined as the proportion of women whom comply with the LOC recommendations they have received (yes, no or partially). Compliance will be analyzed regarding: adequate vitamin D (10 microgram per day) and calcium (1,000 milligram per day) intake, preventive aspirin treatment, and OGTT.

The secondary outcomes are patient satisfaction and cost-effectiveness. These secondary outcomes of Expect Study II will be compared to the outcomes of Expect Study I.

Patient satisfaction will be measured by validated patient satisfaction questionnaires. The Patient Satisfaction Questionnaire Short Form will be incorporated in antepartum surveys two and three. In the postpartum survey, patient satisfaction will be assessed by the Pregnancy and Childbirth Questionnaire (PCQ) [16]. The PCQ is validated for Dutch women who recently gave birth and addresses three topics: women’s satisfaction with the health care professional during pregnancy, health education, and satisfaction with the health care professional during labor. Furthermore, Truijens et al showed the PCQ is sensitive to pick up effects regarding patient satisfaction due to simulation-based obstetric team training [17].

In order to perform cost-effectiveness calculations, we will calculate two incremental cost-effectiveness ratios (ICERs). The first ICER expresses the health care costs per one neonatal composite outcome prevented. The neonatal composite outcome is defined as perinatal death within seven days after birth, asphyxia (Apgar score <7 after 5 minutes), admission to a neonatal intensive care unit within 28 days after birth, SGA (birthweight <2.3 weight percentile), and very preterm birth (birth before 32 completed weeks of pregnancy) [13]. The second ICER will express the health care cost per one maternal gained Quality Adjusted Life Year (QALY).

